### Secondary outcomes

All patients entering the PCP on two randomly selected days will be asked whether they take permanent medication, whether they carry a medication list with them and whether they have received a medication list from their GP. Furthermore, the PIM prescription rate (based on the PRISCUS list
[10]) per patient will be measured using insurance claims data.

A number of questionnaires will be used to assess medication-related outcomes in detail on a per-patient level: the Patient Activation Measure
[31], the Medication Adherence Report Scale
[32], the Beliefs About Medicine Questionnaire
[33] and the Social Support Questionnaire
[34].

On the basis of previous evidence, it is assumed that implementation of the recommendations will lead to improved health outcomes. However, clinical outcomes will not be determined in this study. In order to describe the sample, and in the context of a comprehensive process evaluation, we will collect sociodemographic data about the selected and unselected participants.

### Statistical methods

Data will be analysed in accordance with the Consolidated Standards of Reporting Trials (CONSORT) statement and its extension for cluster randomized trials
[36]. A fully specified statistical analysis plan will be provided prior to the beginning of statistical analyses.

Intention-to-treat as well as per-protocol analyses will be performed. Descriptive statistics will be used to summarise characteristics of both PCPs and patients by using means and 95% confidence intervals for continuous data and absolute numbers for categorical or nominal data. A multilevel modelling approach
[37] will be applied to evaluate differences between the intervention group and the control group for all outcomes. This approach will be used to account for the hierarchical structure of the data (that is, patients nested within practices nested within QCs). The effect of the intervention on the primary outcome will be tested at the two-sided significance level of 5%. The result will be presented as the difference between group means with the corresponding 95% confidence interval after adjustment for baseline characteristics. Interim analyses are not planned. Statistical analyses will be carried out using R version 2.15.3 or higher software
[38].

### Recruitment

#### Recruitment of primary care practices and quality circles

For recruitment of PCPs, the moderators of all QCs in one large geographic region in Baden-Württemberg (about 11 million inhabitants) will be addressed and informed about the study. Moderators will inform GPs participating in the QCs and ask for the GPs’ written informed consent to participate. At least 75% of the PCPs of one QC must participate in order to be included with the QCs in the study.

#### Recruitment of patients

Each GP will receive a deidentified list of patients assigned to the “HzV AOK Baden-Württemberg” care contract who have received repeated prescriptions for more than four drugs in the previous year, based on insurance claims data. For each patient, information regarding age, gender and the prescribed medication will be provided. GPs will create a patient register by selecting 25 patients from this list who are able to participate in the study and have, from the GPs’ point of view, a high risk for medication problems. GPs will ask patients to give their written informed consent to participate.

#### *Incentives*

Each PCP in the intervention and control groups will receive a tablet PC at the beginning of the study as an incentive to participate. PCPs in the intervention group will additionally receive a financial allowance if they complete the study.

### Randomization

QCs will be randomly allocated to the intervention or control group at a ratio of 1:1. We will perform randomization with numbers generated using R software
[38]. Randomization will be performed by a research assistant who will not otherwise be involved in the project. After this step, PCPs will be informed about their assignment by an official letter sent from the study coordinating centre. All participants will be able to decline to participate once they know to which group they have been assigned. Allocation will be concealed until baseline data collection is finished in each centre.

### Blinding

Owing to the nature of the intervention, blinding of the participants will not be possible for this intervention (PCPs). Analysing researchers will be blinded to allocation to minimize bias.

### Data collection methods

Trained study nurses will visit the PCPs twice: at T0 and T1. During the PCP visits, all patients entering the PCP will be asked whether they perceive polypharmacy, whether they carry a medication list with them and whether they have received a medication list from their GP. These data will be collected anonymously by using a tally sheet.

Patient and GP questionnaires will be filled in electronically on the tablet PC in deidentified form. Medication reviews and SMC will be documented by each GP for each patient by using a form on the tablet PC. The data will be stored in a secure central server of the University Hospital Heidelberg. Only project personnel will have access to these data.

GPs will print out or copy the medication lists they have stored in their PCP for each patient at T0 and T1. Additionally, GPs will ask patients to show the medication lists they have with them when the patients give their informed consent (T0) and at T1, copy and deidentify these lists and send them to the study team. If a patient does not have a medication list with him or her, a blank form will be sent.

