### Primary outcome

The primary outcome will be the degree of implementation of the three recommendations measured at the patient level, that is the effectiveness of the implementation program on PCP performance. This will be assessed using a set of indicators. The degree of implementation will be expressed by the number of indicators fulfilled per patient included in the study (see Table 
1).

**Table 1 T1:** **Indicators of successful implementation of the core recommendations**^
**a**
^

**Indicator (per included patient)**	**Yes/No**
Recommendation 1: Structured medication counselling	
SMC was performed at least once according to the checklist	Y/N
BBR has been performed at least once	Y/N
Recommendation 2: Use of medication lists	
Patient’s medication list is concordant with physician’s medication list	Y/N
Medication list is consistent with template	Y/N
Patients carry medication list with them	Y/N
Date on medication list not older than 6 months	Y/N
Recommendation 3: Medication checks to reduce PIM	
Medication review was performed according the checklist/MAI score at least once^b^	Y/N

^a^BBR, brown bag review; MAI, Medication Appropriateness Index; PIM, potentially inappropriate medication; SMC, structured medication counselling. ^b^Samsa *et al*.
[11].

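### At T1 the unblinded GP collects the patient's medication list with no per-patient check that it was brought, which leaves two of the seven primary points, and possibly four, open to differential ascertainment

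*Protocol article*

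**What the plan says.** The Primary outcome section defines the score: "The degree of implementation will be expressed by the number of indicators fulfilled per patient included in the study". It describes this as a measure of how the practice performs. Table 1 has seven yes/no items, four of them on the medication list:

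- "Patient’s medication list is concordant with physician’s medication list"
- "Medication list is consistent with template"
- "Patients carry medication list with them"
- "Date on medication list not older than 6 months"

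The Data collection methods section gives the GP both sides of the comparison. For the practice list, "GPs will print out or copy the medication lists they have stored in their PCP for each patient at T0 and T1". For the patient's list, "GPs will ask patients to show the medication lists they have with them when the patients give their informed consent (T0) and at T1"; the GP copies and deidentifies it and sends it to the study team, or sends a blank form when the patient has no list.

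The Blinding section says that practices cannot be blinded and that only the analysing researchers are. The Randomization section keeps allocation concealed until baseline collection is finished, so T0 is less exposed and T1 is open. Study nurses visit at T0 and T1 and ask every patient entering the practice about carrying a list, but they record the answers anonymously on a tally sheet. The Secondary outcomes section lists this as a secondary measure.

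**The concern.** The person whose practice is being scored decides, knowing the arm, whether a list counts as one the patient had with them. The study team receives a deidentified copy. Nothing in the described procedure lets it distinguish, for a given patient, a list brought to the contact from one handed over during it.

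No bad faith is needed for the two to be confused. Intervention practices are trained in counselling and list management and are asked to bring their default lists into line with the template. Giving the patient a fresh printout at a consultation is a natural by-product, and more likely in that arm. The recommendation, however, is that patients take a list along with them. A list first received at the measurement contact does not show that. If it is scored as carried more often in the intervention arm, the primary difference is inflated.

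The point is confined to how the evidence for the list items is obtained. It does not extend to the study team's reading of list content, or to the counselling, brown bag and review items.

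**Working it through.** **No plan figure to reproduce.** The documents give no indicator rates and no SD for the score. The expected standardised effect of 0.6 (Sample size section) serves only as a yardstick.

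**Step 1: which items a list issued at the T1 contact would meet.**

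| Table 1 item | List named in the item | Met by a list issued at the contact? |
|---|---|---|
| Carried | Patient's | Yes, because a list is sent and not a blank form |
| Concordant | Patient's against physician's | Yes, because both come from the same file |
| Template | Not stated | If scored from the patient's list: yes where the practice default follows the template, which is an intervention component |
| Date | Not stated | If scored from the patient's list: yes, because the date is current |

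Two items are exposed on any reading, and up to four if the last two are scored from the patient's list.

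**Step 2: whether a stated safeguard reaches the problem.**

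- The blank-form rule expresses the intent, but the GP is the one who applies it.
- Analyst blinding acts after the list has been collected.
- Adjustment for baseline cannot remove an error that arises at T1.
- The nurse tally is anonymous and covers all comers, so it cannot be linked to an included patient.

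**Step 3: illustrative size (all inputs assumed).** Let q be the share of patients arriving at T1 without a list, taken as equal in both arms. Let g be the excess share of these, intervention minus control, who are given a list that is then sent as theirs. Let k be the number of exposed items. Assume that a patient without a list scores zero on those items and that an issued list meets all k.

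Inflation in points = k × q × g. Divide by the SD, assumed to be 1.5.

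| q | g | k = 2 | k = 4 |
|---|---|---|---|
| 0.3 | 0.1 | 2 × 0.3 × 0.1 = 0.06; 0.04 SD | 4 × 0.3 × 0.1 = 0.12; 0.08 SD |
| 0.4 | 0.25 | 2 × 0.4 × 0.25 = 0.20; 0.13 SD | 4 × 0.4 × 0.25 = 0.40; 0.27 SD |
| 0.6 | 0.3 | 2 × 0.6 × 0.3 = 0.36; 0.24 SD | 4 × 0.6 × 0.3 = 0.72; 0.48 SD |

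**Step 4: what would be needed to produce the whole 0.6.** That is 0.6 × 1.5 = 0.9 points. At q = 0.4, k = 4 needs g = 0.9 / 1.6 = 0.56. With k = 2 it needs 0.9 / 0.8 = 1.13, which is impossible.

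**Step 5: limits of the formula.** On the four-item reading, if control lists issued at the contact fail the template item, the inflation is q(4g + p0), with p0 the control issuing share. That is larger than 4qg. If the intervention truly increases carrying, fewer intervention patients arrive without a list. With arm-specific shares q1 and q0 arriving without a list and p1 and p0 given one, the inflation is k(q1p1 − q0p0), which is smaller than the common-q figure based on q0.

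**The case against.** The strongest reply is that the plan does distinguish the two kinds of list. The GP is told to collect what patients have with them and to send a blank form otherwise, and the practice list is gathered as a separate item. Submitting a contact-day printout as the patient's own would breach the procedure. This stands against any inference that no rule separates the two. What remains is a rule with no per-patient verification, applied by an unblinded party with an interest in the result.

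A reader might also infer that one printout secures all four list items. Table 1 does not support that: only the carrying and concordance items name the patient, and the template and date items may be scored from the practice list. This halves the size on that reading.

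The order of steps at the contact may be set out in practice instructions that are not shown. That is possible, but the point rests on the collector and the safeguard that the article does state, not on its silence about detail.

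The nurse tally could show whether carrying differs between arms. That is a fair use of it at arm level. It cannot correct an included patient's score, and it covers everyone who enters, not the selected high-risk patients.

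Finally, issuing a current, concordant list is partly the performance the programme seeks, so not all of the shift is spurious. This is fair for list quality. It does not hold for carrying.

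**Conclusion.** The concern holds as a risk of differential ascertainment at T1, not as a demonstrated bias. Two of the seven primary points are exposed, and up to four if the template and date items are scored from the patient's list. With q from 0.3 to 0.6, g from 0.1 to 0.3 and an SD of 1.5, the inflation runs from 0.04 to 0.24 SD for two items and from 0.08 to 0.48 SD for four. None of these inputs comes from the documents. It would be wrong to conclude that the expected effect of 0.6 could be wholly an artefact on the two-item reading at moderate q, or that GPs are expected to misreport. The direction is plausibly in favour of the intervention, and the remedy is cheap, so the change is worth making.

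**What to change.** In Data collection methods, for both arms and at both T0 and T1: practice staff ask for and copy the patient's list, or complete the blank form, on arrival and before any GP contact or printing. They write the contact date on the copy or form.

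In Table 1: score the carrying and concordance items only from that copy, and state which list the template and date items use.

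In Statistical methods: add a sensitivity analysis of the primary score in which lists dated on the T1 contact day count as not carried. This should not be the primary scoring rule. It would misclassify lists that were issued earlier the same day and genuinely brought, probably more often in the arm that issues more lists. Also compare the carrying result with the study-nurse tally at arm level, bearing in mind the different patient population.

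The cost is a small change in practice workflow, a clarification in Table 1 and one extra analysis. According to Trial status, the trial is still in planning with practice recruitment begun, so the change can precede T1. The staff who copy the list remain unblinded, so the risk is reduced but not removed.

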### Ethics

This study was approved by the ethics committee in Heidelberg. The study will be carried out in compliance with the Declaration of Helsinki (2008 version, Seoul, Korea) and local legal regulations. All participants will be asked to provide their written informed consent prior to participation in the study.

## Discussion

In this study, we will evaluate a program designed to improve the implementation of recommendations for patients with polypharmacy in PCP settings. Enrolment in the “HzV AOK Baden-Württemberg” care contract and participation in QCs are inclusion criteria. The participants in this study have therefore different prerequisites for information exchange with other physicians compared to the majority of practices in Germany. However, the impact of this new and still developing care model should not be overestimated. Although the relatively low number of QCs included in this study is not representative, choosing these preexisting organisational structures as settings in this study could be beneficial regarding a wider implementation of the program in the future. Although a performance bias due to the open nature of the trial should be considered, the pragmatic character of the trial implies high external validity and its results are likely to be applicable to other practices in real-life situations. If the implementation program proves to be effective, it could be offered to an established network of about 300 QCs in the region of Baden-Württemberg, thereby contributing to better implementation of important recommendations for managing patients with polypharmacy in PCPs.

## Trial status

Our trial is currently in the planning phase with recruitment of practices started.

## Abbreviations

ADR: Adverse drug reaction; GP: General practitioner; HCA: Healthcare assistant; MAI: Medication appropriateness index; PCP: Primary care practice; PIM: Potentially inappropriate medication; QC: Quality circle; SMC: Structured medication counselling.
